#### Procedure

In the first randomization, patients will be randomized into two groups at baseline. The control group (ie, the app-only [A] group) will have the smartphone app with no visualization, and the intervention group will have the app with text information only as in the current Medication Guide (AT) [43]. At 4 weeks, patients from both the control and intervention groups from both arms, who have scores of 80% or higher in the information recall survey, will continue in the study with the same intervention, in either the A or AT group. Those who do not meet the performance cutoff will be rerandomized further into two groups for each arm. In the second randomization at 4 weeks, the control group from the first arm (A) will have the smartphone app with just text information about medication (AT), and the intervention group will have the smartphone app with the prototype of medication information visualization (AV). The control group from the second arm (AT) will have the app with contextual medication information in a text format (ACT), and the intervention group will have the app with our visualization design (AV). This part of the study will continue for 8 weeks. The monitoring is not a continuous process. Only the principal investigator will have access to the main file and will check the adherence and patient analytics at 4 and 8 weeks.

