#### Data Collection

We will collect demographics data at baseline. Data will be collected at 4 and 12 weeks. The 12-week time point will be considered the primary endpoint for the study. The AI platform on the smartphone app’s back end will provide patient analytics on the usage of the mobile app (ie, intake of medications in the app diary and access frequencies).

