#### Data Analysis

Demographic information will be presented using descriptive statistics. We will analyze the groups using *t* tests to detect differences between the means for continuous data. Chi-square analysis will be used to evaluate differences between arms for primary and secondary outcomes. We will use the univariate analysis of variance to calculate the mean differences between groups. If the distribution is not normal, we will use general linear modeling for the data analysis [47,48]. The AI-based analytics data from the smartphone will show us the patients' medication intake and we will correlate that score with our interventions.

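### Aim 3 relates one app-diary adherence score to the interventions without limiting it to time after the week-4 re-randomization, so the AT:AV and ACT:AV differences may be diluted

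*Protocol article*

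**What the plan says.** All places are in the protocol article, Aim 3.

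- **Procedure, first stage.** "In the first randomization, patients will be randomized into two groups at baseline": app only (A) or app with the Medication Guide text (AT).
- **Procedure, week 4.** Patients who reach the recall cut-off of 80% "will continue in the study with the same intervention, in either the A or AT group". The others are randomized again. For those who began on A: "In the second randomization at 4 weeks, the control group from the first arm (A) will have the smartphone app with just text information", and the comparison group receives AV. For those who began on AT: "The control group from the second arm (AT) will have the app with contextual medication information in a text format (ACT"), again against AV. On duration: "This part of the study will continue for 8 weeks".
- **Data Collection.** The app's back end records "intake of medications in the app diary and access frequencies". Data are collected at 4 and 12 weeks, and "The 12-week time point will be considered the primary endpoint for the study".
- **Procedure, monitoring.** The principal investigator checks adherence and app analytics at 4 and 8 weeks.
- **Study Measures.** The diary is one of two components of the secondary outcome, medication adherence. The other is the MMAS-8.
- **Data Analysis.** The only sentence on analysing the diary says that it will show patients' "medication intake and we will correlate that score with our interventions".

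None of these sections says when the diary starts or which weeks make up the score.

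**The concern.** A re-randomized patient receives two conditions in turn: A then AT, A then AV, AT then ACT, or AT then AV. A single diary score related to the interventions does not say which of the two conditions it describes.

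In the AT:AV and ACT:AV contrasts, which the second randomization exists to test, weeks 0-4 come before that randomization and cannot carry its effect. If those weeks are included in the score, they add shared time with no treatment difference and pull the observed difference toward zero. A real effect of the visualization on logged intake would then be understated and harder to detect.

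The first four weeks are also useful information that the stated analysis leaves aside. For each re-randomized patient they are a measure of the same outcome taken before randomization.

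**Working it through.** **Inputs from the article.** First stage: weeks 0 to 4. Second stage: 8 weeks, so weeks 4 to 12. Second-stage groups: 100 each, 80% power, 5% level (Sample Size Justifications).

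**The article's own figure.** Four second-stage groups of 100 make 400. Then 400 × 1.11 / 0.5 = 888, as stated, so 100 per group is indeed the size of each second-stage contrast. That calculation is for a 1-point Likert difference. The article adds a power statement for the MMAS-8 and none for the diary.

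**Step 1: share of the score that precedes the re-randomized condition.** Share = weeks before re-randomization / weeks in the score.

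| Window of the score (not stated) | Share before the condition | Share of the effect retained |
|---|---|---|
| Weeks 0-12 | 4/12 = 33% | 8/12 = 67% |
| Weeks 0-8 | 4/8 = 50% | 4/8 = 50% |
| Weeks 4-12 | 0/8 = 0% | 100% |

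The last column assumes a constant weekly effect from week 4 and equal weight for each week. The shares apply to patients moved to AV or ACT, and to those moved from A to AT. For patients who stay on A or AT the share is 0% in every window.

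**Step 2: what dilution could mean for power (illustration only).** Assume a contrast with exactly 80% power at 100 per group on the weeks 4-12 score, two-sided 5%.

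- Expected z for the undiluted contrast: 1.960 + 0.842 = 2.802.
- After dilution with the same SD: 2.802 × 8/12 = 1.868. Power = Φ(1.868 − 1.960) = Φ(−0.092) = 46%.
- A 12-week mean varies slightly less than an 8-week mean. With equal correlation ρ between weeks, the expected z is multiplied by √{[ρ + (1−ρ)/8] / [ρ + (1−ρ)/12]}.
  - ρ = 0.3: √(0.3875/0.3583) = 1.040; z = 1.942; power 49%.
  - ρ = 0.5: √(0.5625/0.5417) = 1.019; z = 1.903; power 48%.
  - ρ = 0.9: √(0.9125/0.9083) = 1.002; z = 1.872; power 46%.

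So power is about 46-49% for ρ from 0.3 to 0.9. With a much weaker correlation, so that half the variance of the 8-week mean is within-patient noise (ρ = 1/9), the variance ratio is 0.5 + 0.5 × 8/12 = 0.833. Then z = 1.868/√0.833 = 2.046 and power is 53%.

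**Step 3: the timing statements.** Procedure has analytics checked at 4 and 8 weeks; Data Collection has data taken at 4 and 12 weeks. If the 8 weeks are counted from re-randomization, 4 + 8 = 12 and the two agree. If they are counted from baseline, the last check falls halfway through the second stage. The text does not say which is meant.

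**The case against.** The strongest objection is that no sentence says the score starts at baseline. A whole-study window is an inference, and the week-4 check would fit a score split by stage just as well. A scoring window is also a detail that an article commonly leaves to the full protocol or analysis plan. The first part stands: the 33% is conditional on a weeks 0-12 window, and the share could be anything from 0% to 50%. The second part stands only in part. The article does state an analysis for this outcome, and that analysis relates one score to interventions that many patients receive in sequence. As worded, it does not fit the two-stage design.

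Three stronger readings are tempting, and the document does not support them.

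- **That a general decline in diary use would look like an intervention effect.** If every patient is scored over the same weeks, a common decline enters all groups equally. Patients who stay on A or AT do differ from those re-randomized, but because they were selected on recall, not because of the diary window.
- **That the diary analysis loses power from a planned 80%.** The 80% belongs to the Likert and MMAS-8 outcomes. The article gives no effect, SD or power for the diary.
- **That the result would be biased toward one condition.** In the randomized contrasts the shared first-stage weeks only dilute the difference.

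**Conclusion.** The point holds in a conditional and minor form. The diary score is tied to the interventions with no restriction to time after the week-4 re-randomization, and its window is not stated. If the window is weeks 0-12, one third of a re-randomized patient's score precedes the condition tested, and the AT:AV and ACT:AV differences appear at about 67% of their true size. This rests on a constant weekly effect and on diary recording from baseline. The latter is very probable, since all patients have the app then and analytics are checked at week 4, but it is not stated. The direction is toward no difference. The 46-49% power figure only shows how much a one-third dilution can matter; it does not describe a power claim in the plan. The 12-week comprehension endpoint and the MMAS-8 are unaffected.

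**What to change.** 1. In Data Analysis, define the diary score for the AT:AV and ACT:AV contrasts as covering the week-4 re-randomization to week 12 only.
2. Replace the unadjusted correlation for these contrasts with a comparison of the randomized groups, made separately within each first-stage arm, with the same patient's weeks 0-4 diary score as a covariate. Patients who were not re-randomized do not enter these two contrasts.
3. State whether the 8-week analytics check in Procedure is counted from baseline or from re-randomization, and reconcile it with data collection at 4 and 12 weeks.

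The cost is wording only. Study Measures describes a daily intake diary, so provided it is recorded from baseline both windows can be taken from data the app already holds. No extra visit, survey or patient is needed.

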#### Study Measures

The following study measures will be conducted:

Medication information comprehension from the first survey (primary outcome) [45]; the comprehension measure will be a composite of three subscales:Relevance to understanding patients’ attitudes,Patients’ levels of confidence and knowledge of medication use, measured using a Likert scale, andInformation recall subscale, measured using a dichotomous scale (ie, true or false).Survey on patients’ perceptions of medication information.Medication adherence (secondary outcome) will be operationalized by the following:MMAS-8 [46] survey score; the dichotomous response categories are yes or no for each item, andAnalytics of the patients’ daily intake of medications diary from the smartphone app.

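### The in-app diary part of the adherence outcome can reflect logging rather than intake, and correlating it with the several app conditions defines no randomised contrast

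*Protocol article*

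**What the plan says.** All references are to Aim 3 of the protocol article.

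- **Study Measures** gives adherence two components without ranking them: "MMAS-8 [46] survey score; the dichotomous response categories are yes or no for each item", and analytics of the "daily intake of medications diary from the smartphone app".
- **Data Collection** describes the diary data as app usage. The back end "will provide patient analytics on the usage of the mobile app (ie, intake of medications in the app diary and access frequencies"). Data are collected at 4 and 12 weeks, and week 12 is the primary endpoint.
- **Data Analysis** reads the same data as showing intake and adds: "we will correlate that score with our interventions". It also states: "Chi-square analysis will be used to evaluate differences between arms for primary and secondary outcomes".
- **Intervention** and **Procedure** define the conditions as different contents of one app: app only (A), Medication Guide text (AT), contextual text (ACT) and interactive visualisation (AV). Patients who score below 80% on recall at week 4 are re-randomised to AT or AV in the first arm, and to ACT or AV in the second.
- **Sample Size Justifications** sizes adherence on a 1-point MMAS-8 improvement, calls the MMAS-8 the secondary outcome, and names the pairs AT:AV and ACT:AV. It sizes no diary effect.

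**The concern.** There are two separate problems, both limited to the diary.

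**Measurement.** A diary entry needs a dose taken and a patient who opens the app and records it. The randomised conditions change what the patient finds in that app, and the Discussion presents engaging the user as a purpose of the work. Nothing in the article separates a dose not logged from a dose not taken. More frequent logging under AV would therefore look like better adherence.

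**Analysis.** The interventions are several unordered conditions. A correlation with them needs numeric codes, and the result depends on the codes chosen. Grouping by condition label would also not follow the randomisation. At week 12, AT would hold second-arm patients who stayed on it because they reached 80% recall, together with first-arm patients re-randomised to it because they did not. AV would come from both arms.

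At stake is whether greater app use could be reported as improved adherence, which is part of the Aim 3 hypothesis.

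**Working it through.** **1. The plan's own figure.** Inputs from Sample Size Justifications: 100 per group, four groups (AT and AV, ACT and AV), 50% re-randomised, 11% loss.

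4 × 100 = 400; 400 / 0.50 = 800; 800 × 1.11 = 888.

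This reproduces the stated 888. The figure is built on the two second-stage pairs, and the point made here does not alter it.

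**2. How logging enters the diary score.** If logging is independent of intake, expected diary adherence = true intake × probability that a taken dose is logged. All rates here are assumptions:

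- Comparator: 0.80 × 0.70 = 0.56.
- AV: 0.80 × 0.80 = 0.64.
- False difference: 0.64 − 0.56 = 0.08.

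At equal true intake of 0.80, the false gain is 0.80 × the logging difference. Logging differences of 3, 5, 10 and 15 points give 2.4, 4, 8 and 12 points.

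**3. How often a test would call this significant.** Simulation with 100 per group (from the plan) and 56 days (8 weeks × 7). Assumed: the same true intake distribution in both groups (mean 0.80, SD 0.15), comparator logging 0.60, a t test at 5%, and 4000 runs.

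| Extra logging with AV | Rejections, between-patient logging SD 0.15 | Rejections, SD 0.25 |
|---|---|---|
| 0 points | 5% | 6% |
| 3 points | 17% | 12% |
| 5 points | 42% | 23% |
| 10 points | 93% | 66% |
| 15 points | 99.8% | 94% |

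With equal logging the test keeps roughly its nominal level. Any excess comes from logging alone.

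**4. How coding drives the correlation.** Assume four groups of 100 with mean diary scores 0.5, 0.5, 0.5 and 0.6 and a within-group SD of 0.2. Centred codes are −1.5, −0.5, 0.5 and 1.5, with SD √1.25 = 1.118. The variance of the group means is 0.1² × (1/4) × (3/4) = 0.001875, so the SD of the score is √(0.04 + 0.001875) = 0.2046.

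- Higher group coded at an end: covariance = ±1.5 × 0.1 / 4 = ±0.0375; r = ±0.0375 / (1.118 × 0.2046) = ±0.16.
- Higher group coded in the middle: covariance = ±0.5 × 0.1 / 4 = ±0.0125; r = ±0.05.

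Size and sign both change while the data do not. In one simulated data set with these values, all orderings of the codes gave |r| from 0.01 to 0.13 and p from 0.011 to 0.82. One-way analysis of variance, which ignores coding, gave p = 0.040.

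**5. The two-group case.** For one pair from the same data set, correlation with a 0/1 indicator and the t test both gave p = 0.016. Within a pair, the correlation test is a treatment comparison.

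**The case against.** The strongest reply is that little of the adherence analysis rests on this sentence. The MMAS-8 does not depend on diary logging, the Data Analysis section names between-arm tests for secondary outcomes, and the trial is sized on the MMAS-8. That stands. A reader might infer that the adherence result as a whole is not a treatment comparison, and the documents do not support this.

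Second, in a condensed article the word correlate may only mean relate, and within AT:AV or ACT:AV a correlation is equivalent to a t test. This stands for a pairwise reading. The sentence, however, refers to the interventions in the plural and restricts itself to no pair and no population. The mixing of continuers with re-randomised patients likewise follows only from grouping by condition label, which the article neither states nor excludes.

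Third, no passage reports that AV raises logging. Engagement is an aim with no measured effect, and every condition carries the app, so only differential logging matters. This stands: the bias is a risk and has not been shown.

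Fourth, the Procedure says the principal investigator "will check the adherence and patient analytics at 4 and 8 weeks", which a reader might take as a conflict with the 12-week endpoint. The text describes when the file is looked at. Since the second stage lasts 8 weeks, the 8 may be counted from re-randomisation, which is week 4 + 8 = week 12. At most it needs clarifying.

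Finally, a diary beside a questionnaire is a legitimate pairing, and the MMAS-8 is itself self-reported, with 53% specificity for low adherence in the validation study the article cites. This argues for keeping the diary in a lesser role and against deleting it.

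**Conclusion.** The point holds for the diary component only. The plan classes the data as app usage, then reads them as intake, and ties them to treatment by a method with no defined contrast across A, AT, ACT and AV.

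The size of the measurement problem is unknown. Under the assumptions above, a 5-point logging difference would give a false positive in 23% to 42% of trials, and a 10-point difference in 66% to 93%. These figures, like the 56% versus 64% example, show the mechanism and do not estimate what will happen here. The coding problem needs no assumption about logging: it arises whenever a single correlation is taken over more than two unordered conditions. The MMAS-8 analysis and the 888 total are untouched.

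**What to change.** - **Data Analysis:** replace the correlation by between-group comparisons of diary entries from the second randomisation to week 12, among re-randomised patients, separately for AT versus AV (first arm) and ACT versus AV (second arm). These are the pairs the sample size already names.
- **Study Measures:** name the 12-week MMAS-8 score as the main adherence measure. Report diary entries and access frequency as supportive app-engagement data that cannot alone support an adherence claim, and state that a missing entry is not taken as a missed dose.
- **Procedure:** say what the 4 and 8 weeks of the investigator's checks are counted from.

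**Cost:** no extra patients or data collection. It is more than a change of wording, because the diary loses its standing as a co-equal adherence measure and the adherence claim then rests mainly on a self-reported scale.

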#### Sample Size Justifications

To detect a 1-point improvement on the Likert scale and 80% power at the 5% significance level, the study would require 100 subjects in each group with 1:1 allocation for the second randomization (ie, AT: AV and ACT: AV). To allow for an 11% loss due to dropouts and those lost to follow-up, we would need to recruit 888 patients, allowing up to 50% of the patients to move to the second randomization following the first randomization with a score of 80% or higher in the medication recall questionnaire survey with assigned intervention. Recruitment of 888 patients is also sufficient to detect a 1-point improvement on the MMAS-8 (the secondary outcome), with 80% power at 5% significance. Therefore, our target is to recruit 900 patients.

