#### Limitations

We expect to enroll a large number of patients for this sequential randomized design. We do not anticipate significant problems because our clinics are excellent sites for recruitment. The recruiting advantage is due to the academic affiliations with faculty and residents. However, given our large sample size requirements, to the extent that we cannot recruit around 888 patients, our study will lack rigor.

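### Aim 3 sample size: the 50% re-randomised share is worded as a maximum and tied to high scorers, but the 80% power needs it as a minimum in each first-stage arm

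*Protocol article*

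**What the plan says.** Under Aim 3, Sample Size Justifications, the plan takes a difference of one Likert point as the effect to find, with two-group comparisons AT:AV and ACT:AV after the second randomization. For these it states that "the study would require 100 subjects in each group with 1:1 allocation for the second randomization (ie, AT: AV and ACT: AV"). It then allows for loss: "To allow for an 11% loss due to dropouts and those lost to follow-up, we would need to recruit 888 patients", with the qualifier "allowing up to 50% of the patients to move to the second randomization following the first randomization with a score of 80% or higher". The paragraph ends with a recruitment target of 900.

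Aim 3, Procedure, describes who is re-randomised. At 4 weeks, patients from both arms "who have scores of 80% or higher in the information recall survey, will continue in the study with the same intervention", and "Those who do not meet the performance cutoff will be rerandomized further into two groups for each arm". Low scorers from arm A go to AT or AV, and low scorers from arm AT go to ACT or AV. First-stage allocation is 1:1 (Aim 3, Study Subjects and Recruitment Methods).

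Aim 3, Limitations, judges adequacy by total recruitment alone: "to the extent that we cannot recruit around 888 patients, our study will lack rigor".

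**The concern.** Three things do not fit together.

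- **Direction.** The number available for AT:AV and ACT:AV rises with the share re-randomised. A share used to reach a required number per group must therefore be a minimum. The sentence gives it as a maximum.
- **Who moves on.** Taken as written, the sentence links the second randomization to scores at or above the cut-off. The Procedure keeps those patients on their intervention and re-randomises the others.
- **One share for two arms.** Each comparison draws on one first-stage arm only: AT:AV on arm A, ACT:AV on arm AT. An overall share of 50% does not secure 100 per group in both. The first-stage conditions differ (app alone against app with the Medication Guide text), so equal shares cannot be taken for granted.

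At stake is the power of the two comparisons for which the trial is sized. ACT:AV matters most for interpretation. According to Aim 3, Intervention, both conditions carry the same 10 items, so this comparison separates visual format from content. As the Limitations section stands, the trial could meet its recruitment figure and still fall short in one comparison without the stated criterion showing it.

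**Working it through.** **Inputs from the Protocol article, Aim 3:** 100 per second-stage group, 80% power, 5% significance, 11% loss, a 50% share and a target of 900 (Sample Size Justifications); two second-stage groups per arm, so four in all (Procedure); 1:1 first-stage allocation (Study Subjects and Recruitment Methods).

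**Assumptions, because the document gives no figure:** a two-sided test; the standardised effect d back-solved from 100 per group; loss equal in all groups; arm-specific shares q, which are illustrative.

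**Step 1: reproduce 888.**
- Evaluable re-randomised patients needed: 4 × 100 = 400.
- Evaluable patients overall at a share of 0.50: 400 / 0.50 = 800.
- Loss added: 800 × 1.11 = 888, which matches the plan exactly.

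The division by 0.50 shows the direction. If the share is below 0.50, 800 evaluable patients yield fewer than 400 re-randomised; if it is above, they yield more. This needs no SD.

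**Step 2: per-arm requirement.** Each arm has 400 of the 800 evaluable patients and must supply 2 × 100 = 200. The share must therefore be at least 200 / 400 = 50% in each arm.

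**Step 3: implied effect.** d = (1.960 + 0.842) × √(2/100) = 0.396, or an SD of about 2.52 for a 1-point difference.

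**Step 4: power by share, with 900 recruited.** Evaluable patients per arm: 900 × 0.89 / 2 = 400.5. Patients per second-stage group: n = 400.5 × q / 2. Power = Φ(d × √(n/2) − 1.960).

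| Share q in the arm | n per group | Power |
|---|---|---|
| 30% | 60.1 | 58% |
| 40% | 80.1 | 71% |
| 50% | 100.1 | 80% |
| 60% | 120.1 | 87% |

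If the shares average 50% but split 60/40 between the arms, one comparison has 87% power and the other 71%.

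**Step 5: sensitivity to the assumptions.**
- *One-sided 5% test.* d = (1.645 + 0.842) × √(2/100) = 0.352. The same formula with 1.645 gives 61% at a 30% share, 72% at 40%, 80% at 50% and 86% at 60%, so the pattern holds.
- *A different SD.* With 100 per group and a two-sided test, an SD of 2 would give 94% power and an SD of 3 would give 65%. The level therefore depends on an unstated SD, but the need for at least 50% per arm to reach 100 per group does not.

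**Step 6: recruitment needed for 100 evaluable per group.** 400 / (q × 0.89), with the same share in both arms: 750 at 60%, 899 at 50%, 1,124 at 40%, 1,499 at 30%.

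**Step 7: loss adjustment.** To retain 800 after 11% loss, 800 / 0.89 = 898.9, so 899. With 888 recruited, 888 × 0.89 = 790 remain, or 98.8 per group and 79.5% power. With 900, 801 remain, or 100.1 per group and 80.0% power.

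**The case against.** The strongest defence is that the sentence is garbled rather than wrong. It ends by referring to the assigned intervention, which echoes the Procedure's rule that high scorers stay where they are. Perhaps it meant that up to 50% score 80% or higher and stay. At least 50% would then be re-randomised and the direction would be right. This reading is possible and consistent with the arithmetic, but the words describe patients moving to the second randomization, not staying. A justification that supports two opposite assumptions has to be reworded, and even the favourable reading leaves the share unspecified by arm.

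Three stronger conclusions are tempting, and the document does not support them.

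- **That 80% is the best case.** This follows only from the literal wording. At a 60% share, power is 87%. The Introduction (Background) reports that about half of the participants in one study understood Medication Guide information, and that another found minimal unaided recall. These are different measures and fix no rate here, but they make a share above 50% plausible.
- **That arm AT will have fewer low scorers and ACT:AV will be underpowered.** It is reasonable to expect that the text helps recall, but no arm-specific rate is given. Any split between the arms is an illustration.
- **That 888 shows a materially wrong sample size.** The loss adjustment is not the right form, but it costs about 0.5 points of power and the 900 target already covers it.

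It may also be said that a full table of power by share belongs in the full protocol or analysis plan. That is fair as to detail. The direction of the assumption and the conflict with the Procedure are faults in what this document states.

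**Conclusion.** The point holds. The sample-size paragraph states the re-randomised share in the wrong direction and conflicts with the Procedure on who is re-randomised. Under the Procedure's rule, 100 evaluable patients per group require at least 50% of each first-stage arm to score below 80%. That result rests only on the plan's own figures.

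The size is conditional. On the back-solved effect of about 0.40 and a two-sided 5% test, each drop of 10 percentage points in an arm's share below 50% costs that arm's comparison about 9 to 12 points of power (80% to 71% to 58%), and a rise to 60% gains about 7. The document does not show that the trial is underpowered. It shows that the stated 80% depends on a condition that is misworded and not set per arm. The 888 figure is a minor slip without practical effect on the target.

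**What to change.** 1. **Aim 3, Sample Size Justifications.** Reconcile the sentence with the Procedure. State the assumption as: at least 50% of patients in each first-stage arm score below 80% on the recall survey at 4 weeks and are re-randomised.
2. **Same paragraph.** Say that the 80% power is conditional on this share. Give power at lower and higher shares (for example 30% to 60%) separately for AT:AV and ACT:AV, with the SD and sidedness used.
3. **Aim 3, Limitations.** Tie adequacy to 200 evaluable re-randomised patients per first-stage arm as well as to total recruitment.
4. **Minor.** Replace 888 with 800 / 0.89 = 899 in both sections. The target of 900 stays.

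The cost is a reworded sentence, a short table and one corrected figure. The design and the recruitment target need not change unless the sponsor expects a share below 50% in either arm; step 6 of the working gives the recruitment for that case.
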